**Figure 3 figure3:**
[figure not shown]
Electroencephalogram (EEG) study protocol. (A) Patient undergoes EEG while passively viewing single virtual agents. (B) Patient undergoes EEG while passively viewing combinations of virtual agents.

### Intervention Setting

The first phase of the protocol will start in the 1st Department of Cardiology, AHEPA University Hospital of Thessaloniki, where all clinical assessments (6-minute walk test, questionnaires, clinical assessment, etc) will be completed, and it will continue in a dedicated area in the Laboratory of Medical Physics in the Faculty of Health Sciences of the Aristotle University of Thessaloniki, where patients will undergo the lab study/protocol. After the lab study, some of the patients will be included in the second study situated in their own homes, where they will keep performing their everyday activities. The physical training and e-coaching interventions (phases 2 and 3) will take place at patients’ homes as well.

### Patient Recruitment

According to the protocol, signed informed consent will be obtained by each participant at the baseline visit. It is the investigator’s responsibility to ensure that each study subject is fully informed about the nature and objectives of the study and possible risks associated with participation. The investigator will obtain written informed consent from each subject before any study-specific activity is performed. The investigator will retain the original of each subject’s signed consent document.

### Baseline, Intermediate, and Follow-Up Measurements

Brain Electrical Source Analysis software version 6.0 (BESA GmbH) will be used for data preprocessing. Visual inspection of the recordings will be performed to detect bad channels that will be interpolated using an interpolation algorithm of BESA software. The signal will be band-filtered at 1-30 Hz and a notch filter will be also applied.

Dimensionality of the data will be diminished by using principal component analysis, and an extended independent component analysis [36] will be performed. The reconstructed dataset will then be visually inspected. Subsequently, epochs will be averaged for different stimuli conditions (eg, female, male, old, young, doctors, peers). The randomization graphical user interface (Ragu toolbox [37]) will be used for statistically analyzing the multichannel event-related EEG data. More precisely, the total strength of scalp field differences will be estimated by means of global field power [38], and total count of significant time intervals [39] will be identified by running topographic analysis of variance. Afterward, cortical current density reconstruction will be calculated by low-resolution electromagnetic tomography [40] using BESA software in time intervals that will be derived by the aforementioned analysis.

Statistical parametric mapping will be applied for reslicing and statistical comparison of the current density reconstruction images exported by the BESA software between conditions using the SwE toolbox that applies the sandwich estimator method described by Guillaume et al [41], allowing analysis of longitudinal and repeated measures data. Other biosignals will be compared between conditions (young vs old, female vs male, doctors vs peers) after extracting the grand average values for each condition.

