#### e-Coaching

This is the most important part of the solution (introduced at the last phase of the home study) since it integrates all previous components and their respective information while being the main patient-system interaction point. Daily recommendations about activity and patient self-management together with a virtual coach that will be selected based on findings of the neurophysiological study will be projected on a predefined surface in the patient’s home. The type of messages and time of delivery will be chosen/scheduled based on the personal profile of the patient (eg, nocturnal patterns of activity). Leaving the home environment intact is considered key to increase the acceptance of the e-coaching system by the patient. Therefore, any information visualization will happen only at predefined moments and will disappear instantly, by simply turning the projector off.

An added value of the study is personalization of the e-coaching system by means of evaluating the virtual agent characteristics using EEG, eye gaze tracking, and other physiological measurements.

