### Statistical Analysis

Continuous variables with normal distribution will be reported as mean and standard deviation, while those with nonnormal distribution as median and interquartile range. Categorical variables will be expressed as frequencies and percentages. Continuously data collected will be explored for normality assumption by means of a Shapiro-Wilk test to calculate the appropriate descriptive statistics [47].

Repeated measured analysis of variance or Friedman test will be used to assess changes on continuous data with normal and nonnormal distribution, respectively, between baseline, follow-up, and end-of-study visits. Possible associations between variables will be investigated using Pearson or Spearman correlation coefficients. We estimated sample size conducting power analysis using G*Power software (version 3.1). We performed repeated measures analysis of variance (3 time conditions) using 80% power, a medium effect size of 0.25, and significance level of 5%. The sample size was estimated to be 28 participants. One-third of this patient population that will agree to proceed to home study (phases 1 through 3) will enter the next steps of study protocol [48]. All statistical analyses will be performed using SPSS Statistics version 23.0 (IBM Corp) or R for Windows version 3.1.3 (R Foundation for Statistical Computing).

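### Source-level EEG contrasts are tested in time windows selected by a scalp test of the same contrasts on the same recordings, so their p-values within those windows are too small

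*Protocol article*

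**What the plan says.** The section Baseline, Intermediate, and Follow-Up Measurements of the Protocol article sets out the EEG analysis in order. Epochs are averaged by stimulus condition; the conditions named are gender, age, and doctor versus peer. The scalp data then go through three steps:

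1. **Selection.** The "total count of significant time intervals [39] will be identified by running topographic analysis of variance".
2. **Reconstruction.** Current density is computed by low-resolution electromagnetic tomography "in time intervals that will be derived by the aforementioned analysis".
3. **Test.** Statistical parametric mapping with a sandwich-estimator toolbox is used for "statistical comparison of the current density reconstruction images exported by the BESA software between conditions".

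The source step is described as a statistical comparison, not as a display of where the scalp effect lies. On use of the results, the Methods Overview says the lab findings will shape the phase 3 coaching intervention, and the e-Coaching section refers to a "virtual coach that will be selected based on findings of the neurophysiological study".

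**The concern.** A topographic analysis of variance is itself a test of condition differences. Step 1 therefore keeps the intervals in which the conditions happen to differ most at the scalp. The source images of steps 2 and 3 are computed from that same scalp field. If a window was kept because chance made the difference map large there, the source difference in that window will tend to be large as well. The source-level p-value is calculated as if the window had been chosen without sight of the contrast, so its null distribution is wrong and it is too small.

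At stake is how much weight the source results can bear. They may be reported as evidence beyond the scalp finding when part of that evidence was already used to pick the window. This matters to the extent that source results inform which virtual agent is carried into phase 3.

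**Working it through.** **The plan's own figure.** The Statistical Analysis section states: "The sample size was estimated to be 28 participants". Its inputs are a repeated measures analysis of variance with 3 time conditions, f = 0.25, 80% power and alpha 5%. Correlation and sphericity are not stated; 0.5 and 1 are assumed. Then λ = f² × N × m / (1 − ρ) = 0.0625 × 28 × 3 / 0.5 = 10.5, with 2 and 2 × 27 = 54 degrees of freedom. Power is 0.8125, and 28 is the smallest N that reaches 0.80. The figure reproduces. It has no bearing on the present point except that 28 is the number of participants used below.

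**Why the two statistics are dependent.** Let dᵢ(t) be participant i's difference map between two conditions at time t, and d̄(t) its mean over participants. The scalp step keeps times where the strength of d̄(t) is large relative to sign-flip permutations. With a linear inverse W, the mean source difference in a window is W applied to the window average of d̄(t). Both are functions of the same d̄(t).

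**Size under the null.** Two simulations with no true difference were run, each with 28 participants, one paired contrast and a scalp sign-flip test at 5% per time point. All other settings are assumptions, not figures from the article, which specifies a 128-channel system.

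- *Simulation A:* 32 channels, 30 sources, 200 datasets, 200 permutations, windows of at least 5 consecutive significant samples, Bonferroni correction over sources.
- *Simulation B:* 32 channels, 100 source points, minimum-norm inverse, 199 permutations, longest significant interval only, max-t sign-flip test for family-wise control. Three settings of number of time points and smoothness: B1 (200 points, smoothing 5, 400 runs), B2 (200, 15, 400 runs), B3 (400, 5, 200 runs).

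| Setting | Points p<0.05, fixed window | Points p<0.05, selected | Family-wise rejection, fixed | Family-wise rejection, selected |
|---|---|---|---|---|
| A | 5.0% | 10.9% | 5.5% | 18.4% |
| B1 | 5.3% | 14.4% | 6.8% | 34.0% |
| B2 | 5.2% | 12.5% | 5.0% | 25.5% |
| B3 | 5.0% | 14.1% | 5.0% | 29.2% |

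The fixed-window columns are at nominal within simulation error: for 400 runs the standard error at 5% is √(0.05 × 0.95 / 400) = 1.1 percentage points, and 6.8% is 1.6 standard errors above 5%.

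**From selected windows to all runs (B).** Runs in which no window was found count as non-rejections:

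- B1: 0.815 × 0.340 ≈ 0.28
- B2: 0.470 × 0.255 = 0.12
- B3: 0.975 × 0.292 ≈ 0.285

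**If a global count test at 5% had to be passed first (B).** The gate was passed in 3.7%, 5.2% and 3.5% of runs. Rejection in all runs was then 2.2%, 1.8% and 0.5%. Within gated runs, 17.6%, 14.1% and 17.1% of source points still had p<0.05. Family-wise rejection there was 60%, 33% and 14%, but from only 7 to 21 gated runs per setting, so those three figures are very imprecise.

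**The case against.** **A possible gate.** The article mentions a count of significant intervals. If this is a global test that must be passed before sources are reconstructed, the overall chance of a false source claim under the complete null is held to about 2% or less in the simulations. This stands as a limit on the consequence. It does not remove the defect: the article does not say the count acts as a gate, and the p-values inside selected windows remain too small even with one.

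**Arbitrary magnitude.** Channels, sources, smoothness and window rule are all assumed, and the two simulations differ. This stands. The figures are a range showing direction, and no single inflation factor is a property of this protocol.

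**Own-contrast windows are inferred.** The text does not say in words that each source contrast uses the interval from its own scalp effect. That is true, but it is the plain reading of the sequence, and no other origin for the windows is given.

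**Condensed article.** Thresholds and correction methods may sit in a fuller document, and their absence here is not held against the plan. The point rests on what is stated: a selection rule followed by a formal test on the same data.

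**Stronger readings.** A reader might infer that a chance scalp window is nearly certain to yield significant sources. The simulations contradict this: about 66-82% of selected null windows gave no family-wise significant source. A reader might also infer that the coach will be chosen on inflated p-values. The article does not support that. No section makes a source-level p-value the decision rule, and the e-Coaching section also names eye gaze and other physiological measures. The other biosignals are compared on condition averages, with no mention of the EEG-derived windows.

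**Conclusion.** The point holds for the source-level inference of the lab study. As described, windows are selected on a scalp condition difference and the conditions are then tested at source level on the same recordings. Assuming each contrast uses its own intervals, the resulting p-values in selected windows do not have a 5% error rate. In the settings tried, the share of source points below 0.05 rose from 5% to about 11-14%, and family-wise rejection rose from 5-7% to about 18-34% of selected windows. The family-wise figures are conditional on a window having been selected and should not be read as study-wide false-positive rates; if the interval count gates the source step, the unconditional rate is about 2% or less. The direction was the same in every setting, while the size depends on the assumptions. The sample size and the home-study outcome analyses are not affected. The only route to the home study is through whatever part source results play in choosing the coach.

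**What to change.** **Simplest change.** State that the source maps are descriptive localisation of the scalp effect, reported without confirmatory p-values. This costs a sentence of wording. A second sentence should say whether the interval count is a global test that must be passed before sources are examined.

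**If source-level p-values are wanted, one of these:**

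- Fix the windows before any condition contrast is seen. No new data are needed, but an effect outside the windows will be missed.
- Choose windows from a contrast independent of the one tested, such as the average over conditions.
- Split each participant's trials, for example odd and even, selecting on one half and testing on the other. Part 1 has 128 image trials (Procedures). If levels are balanced, that is 128 / 2 = 64 per level of a two-level factor, and 64 / 2 = 32 per level in each half, so each step has less precision.
- Permute the whole procedure, repeating window selection and source testing in every permutation. This keeps all trials and costs computing time.

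None of these changes the sample size or any study procedure.

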### Clinical Assessment

Patients will be clinically evaluated before entering each of the two studies and on the initiation of each protocol phase (meaning before entering phase 1, phase 2, and phase 3, and at the end of phase 3, which will mark the end of study), completing 4 on-site clinical visits for the impact of each intervention to be assessed.

On the baseline, intermediate, and follow-up assessments, patient clinical condition, quality of life, and health-related costs will be considered. More specifically, blood pressure, heart rate, blood oxygen saturation, and body weight will be measured for the clinical assessment. To assess physical status, the 6-minute walk test and NYHA functional class will be used for exercise intolerance. Patient-related outcomes to be used include the Beck Depression Inventory [42] and the Dukes questionnaire [43]. As for the evaluation of quality of life, the Short Form Health Survey questionnaire [44,45] will be employed. Self-efficacy for exercise behavior scale will be used for evaluation of changes in patient perspectives on exercise [46]. Finally, for health-related costs, the effect on number of hospital admissions along with the effect on health care use (number of primary and secondary care contacts, social care contacts, relevant medication use) will be calculated during all three phases.

Real-world data will be collected continuously (across all phases of the home study) to assess several aspects of the interventions planned. Continuously measured activity levels expressed in daily steps taken by the patient will be compared across the different study phases. Real-life adherence of the HF patients to the proposed intervention will be measured in terms of attendance at the webFitForAll platform using wearable heart rate monitoring data as well as online activity logs and telephone and clinic follow-up. Real-world adherence will be compared within-subjects for the second and third phases of the study. Use analytics (virtual coach used, content and delivery time of messages/recommendations) of the e-coaching system and juxtaposed relevant outcomes (such as activity levels collected by the activity tracker and adherence to the webFitForAll training program given any system logs) will be routinely collected. Patients adherence will be evaluated by measuring attendance at the webFitForAll and heart rate monitoring data as well as by activity logs and telephone and clinic follow-up.

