### At-Home Study Design

#### General Design

BioTechCOACH-ForALL home study is a prospective, multiple baseline across subjects, nonrandomized, single-arm, single-center study following a within-subject design to assess the feasibility and efficacy of the Virtual Coach Program in older age patients with HF. The study will be delivered in three phases, each of them fulfilling a different scope. All participants will go through all study phases. Each phase will allow participants to familiarize themselves with the delivered technology of that phase. A multiple baseline approach will be followed so that the effects of each phase are as isolated to the previous phases as possible, allowing for effect comparison among them. Clinical and quality of life assessment and exercise behavior and attitude will be measured repeatedly in both the baseline phase and the two intervention phases. This way any cause-effect relationships among the intervention and patient outcome measures will be demonstrated.

The study conforms to the ethical guidelines of the 1975 Declaration of Helsinki, all participants will sign informed consent, and the study protocol has been approved by the bioethics committee of the School of Medicine of the Aristotle University of Thessaloniki (Protocol No. 1.45/21.11.2018) and registered at ClinicalTrials.gov [NCT03877328]. The study protocol is structured in a manner that incorporates three different phases, coming one after the other. Each patient will enter the study in the phase 1 and complete their participation in phase 3.

#### Phase 1

Phase 1 introduces the objective measurement technology, the wearable monitoring device. This technology will be running throughout the project’s lifetime and will provide objective information on patient activity. This information, along with the doctor’s baseline and intermediate assessment, will be used as an indicator of the effectiveness of phases 2 and 3.

#### Phase 2

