Phase 2 introduces a joyful way of exercising, allowing patients to exercise in the comfort of their homes. Patients will be assigned a structured recommended schedule with a goal of 3 sessions per week for a total of 36 sessions in 3 months. Frequency and intensity of the training program are indicated by patient functional capacity. All patients will undergo a 6-minute walk test, and their performance will be used for determination of the exercise program. By protocol, patients performing more than 500 meters in the 6-minute walk test at baseline will be prescribed a more intense exercise program in terms of the number of exercise repetitions. The exercise protocol offers 50 minutes of exercise implementing aerobic and resistance endurance exercises including upper and lower extremities. Regular blood pressure and heart rate monitoring will be performed manually by the patient with the use of dedicated devices in time intervals specified in the protocol. Exercises will be implemented as fun, full-body interactions, processed and recognized through a depth-camera–based sensor and computer vision and translated into computer game actions and scenarios integrated within a Web application [14].

#### Phase 3

Phase 3 introduces the coaching aspects, where exergames are introduced and delivered through home surface projection, apart from the personalized recommendations and suggestions (designed by the doctor).

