### Selection Criteria

Subjects must meet all of the inclusion criteria to be eligible for the enrollment:

Male and female patients aged over 55 years with HF of any etiology, with either reduced or preserved ejection fraction, diagnosed according to international guidelines [7]Must be in New York Heart Association (NYHA) functional class II-IVMust be in stable clinical condition and on stable medical treatment for the underlying disease for at least 3 months prior to inclusion to the studyMust be willing and able to comply with scheduled visits, treatment plan, and trial proceduresMust provide personally signed and dated informed consent document indicating that the subject has been informed of all pertinent aspects of the study

Subjects presenting with any of the following will be excluded from the study:

Unstable disease with evidence of decompensation, recent hospitalization, or undergoing investigation for clinical deteriorationRecent history of chest pain, palpitations, light-headedness, dizziness, or syncope on exertionContraindications to physical activity or with physical obstruction to perform the prescribed training program (eg, patient uses wheelchair)Any severe acute or chronic medical or psychiatric condition that may increase the risk associated with trial participation or interfere with interpretation of trial resultsInvestigational site staff members directly involved in the conduct of the trial and their family members; site staff members otherwise supervised by the investigatorParticipating in any other experimental studiesNot willing to provide signed informed consent

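### Change in hospital admissions across phases cannot be called an intervention effect, because every patient's exposure to the intervention rises together with time since a stability screen

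*Protocol article*

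**What the plan says.** Clinical Assessment lists, "for health-related costs, the effect on number of hospital admissions along with the effect on health care use" (primary and secondary care contacts, social care contacts and relevant medication use), which "will be calculated during all three phases".

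General Design describes a "nonrandomized, single-arm, single-center study following a within-subject design". The order is fixed: "Each patient will enter the study in the phase 1 and complete their participation in phase 3". It names one safeguard: "A multiple baseline approach will be followed so that the effects of each phase are as isolated to the previous phases as possible". Of the repeated measurements over baseline and intervention phases it says: "This way any cause-effect relationships among the intervention and patient outcome measures will be demonstrated".

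Selection Criteria require patients to be in "stable clinical condition and on stable medical treatment for the underlying disease for at least 3 months prior to inclusion", and exclude decompensation and recent hospitalization. How recent is not quantified.

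Phase 2 has "a goal of 3 sessions per week for a total of 36 sessions in 3 months". The Results sections expect phases 2 and 3 to be completed within 6 months. The article text gives no length for phase 1. Strengths and Limitations concedes that there is no distinct control group.

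**The concern.** The entry criteria select on a state closely tied to one of the outcomes. A patient who has been stable for 3 months and not recently hospitalized is less likely to be admitted soon afterwards than later on, when that selection has worn off. Phase 1, the reference without exergames or coaching, is the home phase closest to the screen; phases 2 and 3 lie further away. Because the order is the same for everyone and there is no concurrent control, time since screening and exposure to the intervention rise together in every patient.

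The probable direction is against the intervention: a rise in admissions could appear without any harm, or could cancel a real reduction. With few events, little or no change would also say little. In neither case does the phase contrast estimate what the word 'effect' promises.

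**Working it through.** **Number of patients.** Statistical Analysis gives 28, from a repeated measures ANOVA with 3 time conditions, f = 0.25, 80% power and 5% significance. This reproduces: λ = n·m·f²/(1−ρ) = 28 × 3 × 0.0625/0.5 = 10.5 with 2 and 54 degrees of freedom gives power 0.812, and 28 is the smallest n to reach 0.80. The correlation ρ = 0.5 and sphericity are assumptions, since the article states neither. The calculation is for a continuous outcome and says nothing about admissions.

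The same section sends one-third to the home study: 28/3 ≈ 9. Intervention Setting agrees that only some patients continue. The Abstract and Patient Population can be read as all 28. Both are carried below.

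**Expected admissions per phase.** Assumptions: each phase lasts 3 months (stated only for phase 2); the rate r is 0.2, 0.5 or 1.0 admissions per patient-year (the article gives none); counts are Poisson. Expected count = n × 0.25 × r, and P(none) = exp(−expected count).

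| n | Patient-years per phase | r | Expected | P(none) |
|---|---|---|---|---|
| 9 | 2.25 | 0.2 | 0.45 | 64% |
| 9 | 2.25 | 0.5 | 1.13 | 32% |
| 9 | 2.25 | 1.0 | 2.25 | 11% |
| 28 | 7 | 0.2 | 1.40 | 25% |
| 28 | 7 | 0.5 | 3.50 | 3% |
| 28 | 7 | 1.0 | 7.00 | 0.1% |

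**What the screen alone could do.** Suppose the intervention does nothing and the phase-1 rate is a fraction k of the later rate, with k of 0.75, 0.5 or 0.25 (also assumed). The expected rise from phase 1 to a later phase is D = n × 0.25 × r × (1−k), and the SD of the difference is √[n × 0.25 × r × (1+k)].

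| n | r | k | Phase 1 | Later phase | D | SD | P(rise) | P(fall) |
|---|---|---|---|---|---|---|---|---|
| 9 | 0.5 | 1 (no selection) | 1.13 | 1.13 | 0 | 1.50 | 0.36 | 0.36 |
| 9 | 0.5 | 0.5 | 0.56 | 1.13 | 0.56 | 1.30 | 0.49 | 0.18 |
| 9 | 1.0 | 0.25 | 0.56 | 2.25 | 1.69 | 1.68 | 0.76 | 0.08 |
| 28 | 0.5 | 0.5 | 1.75 | 3.50 | 1.75 | 2.29 | 0.71 | 0.16 |
| 28 | 1.0 | 0.25 | 1.75 | 7.00 | 5.25 | 2.96 | 0.95 | 0.02 |

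Over the whole grid with k below 1:

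- At n = 9, D runs from 0.11 to 1.69, and D/SD from 0.11/0.89 = 0.13 to 1.69/1.68 = 1.0.
- At n = 28, D/SD runs from 0.35/1.57 = 0.22 to 5.25/2.96 = 1.77.

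So with about 9 patients the artefact tilts the direction but is mostly no larger than chance; with 28 it is more visible. No significance test is applied, because the article states none for admissions.

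**The case against.** The article is candid about much of this. It calls itself a single-case series without a distinct control group, plans analysis on an individual basis, and names a multiple baseline approach. Utilization is the last item in a list of assessments, with no hypothesis, test or power attached. At about 9 patients chance swamps the artefact, and presenting counts per unit of time is commonly left to an analysis plan.

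Most of this stands as a limit on the point. A significance threshold for admissions would test an analysis that nobody has proposed. The objectives concern adherence, activity, engagement and e-coach development, so there is no health-cost objective to fail. The missing phase-1 length and time denominator are not faults of a condensed article.

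It does not answer the core. Baselines of clearly different lengths could in principle put patients in different phases at the same time since screening. But the article gives no stagger length, every patient still passes the screen before phase 1, and an expected 0.5 to 2.3 admissions per phase leave almost nothing to compare. Admitting that there is no control group, and describing context and participants, does not remove the confounding while the text still speaks of an effect and of demonstrated cause and effect.

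A reader might go further and infer that phase 1 is artificially low and that the natural course of heart failure drives any change. The documents do not support that: they give no admission rate, no phase-1 length and no definition of recent. Intervention Setting also places the lab visit between the first assessments and the home study, with no interval stated.

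**Conclusion.** The plan is wrong as written on this outcome. In a single-arm, fixed-order design that enrols on stability and no recent hospitalization, change in admissions is confounded with time since the screen, so no intervention effect on admissions can be drawn from it.

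The likely direction is to mask a benefit or suggest harm. The size is unknown: the tables rest on assumed rates, assumed 3-month phases and an assumed depression of the phase-1 rate, and only show how few events there would be (about 0.5 to 2.3 per phase with 9 patients, 1.4 to 7 with 28).

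The selection argument is made for admissions. A reader might extend it with equal force to care contacts and medication use, but there it is only an inference, because the entry criteria do not select on contacts. Those items share the lack of a control and the fixed order, so the word 'effect' is too strong for them too.

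**What to change.** In Clinical Assessment, replace the effect on admissions and health care use with wording such as:

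> Hospital admissions and health care contacts will be summarized descriptively as events per patient-month in each phase, with the patient-months shown. No intervention effect on health care utilization or cost will be concluded. Admissions in phase 1 may be low because patients are enrolled after at least 3 months of stability and without recent hospitalization.

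The word 'may' is deliberate, since the documents do not show that phase-1 admissions are in fact depressed. In General Design, except utilization from the statement that cause-effect relationships will be demonstrated.

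The cost is wording only: no new data, visits or patients. The sponsor gives up a claim that the design cannot support.
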